### 2.8. Outcome Hierarchy

Consistent with the pilot and feasibility focus of the present study, feasibility and acceptability outcomes were evaluated in terms of recruitment, consent, retention, intervention attendance and adherence, completeness of outcome assessments, intervention fidelity, withdrawals, and adverse events.

For the clinical outcomes, the hierarchy reported in the trial registry (ANZCTR; ACTRN12626000148370) was retained. The registered primary clinical outcomes were spinal mobility assessed using the IDIAG M360 system and respiratory function assessed using maximal inspiratory pressure (MIP), evaluated at baseline and after the 8-week intervention. Registered secondary outcomes included salivary cortisol concentration, myotonometric measures of tissue tone and stiffness, musculoskeletal symptoms, health-related quality of life assessed using the 36-Item Short Form Health Survey (SF-36), and psychological well-being assessed using the World Health Organization Five Well-Being Index (WHO-5).

Given the pilot nature and limited sample size of the study, analyses of these clinical outcomes were intended to provide preliminary estimates of potential changes rather than confirmatory evidence of intervention effectiveness. The schedule of enrolment, interventions, and assessments is presented in Table 2, the outcome hierarchy and analysis framework are summarized in Table 3, and the intervention and control conditions are summarized in Table 4.

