## 4. Subjective Outcome Measures (Pre–Post)

Musculoskeletal symptoms were assessed using the Nordic Musculoskeletal Questionnaire (NMQ) across nine body regions: neck, shoulders, upper back, elbows, wrists/hands, lower back, hips/thighs, knees, and ankles/feet. NMQ-7 assessed symptoms during the previous 7 days and was treated as an exploratory pre–post symptom indicator. Because the six-month recall period extended substantially before the eight-week intervention, NMQ-6 was used only as descriptive contextual information concerning the broader history and anatomical distribution of symptoms and was excluded from analyses intended to represent change during the intervention. Binary symptom indicators were summarized using counts and proportions. The NMQ measures occurrence and distribution rather than symptom intensity.

Pain intensity was assessed separately using the Visual Analogue Scale (VAS). The scale ranged from 0 to 10, where 0 represented no pain and 10 represented the worst imaginable pain. Participants indicated the intensity of their perceived pain on the scale.

Psychological well-being was assessed using the World Health Organization Five Well-Being Index (WHO-5), a five-item self-report measure of subjective psychological well-being. Each item was scored from 0 to 5, resulting in a raw total score ranging from 0 to 25, with higher scores indicating better well-being. In the present study, the raw 0–25 score was used.

Health-related quality of life was assessed using the 36-Item Short Form Health Survey (SF-36). The questionnaire evaluates eight domains: physical functioning, role limitations due to physical health, bodily pain, general health perceptions, vitality, social functioning, role limitations due to emotional problems, and mental health. Higher domain scores indicate better health-related quality of life.

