### 4.2. Statistical Analysis

Statistical analyses were performed in R 4.3.2 after study completion. The primary quantities of interest were the feasibility proportions for recruitment, consent, retention, attendance/adherence, and outcome completeness. Clinical analyses were secondary and exploratory. The target exploratory contrasts were CST versus CG, RT versus CG, and CST versus RT for change from baseline to 8 weeks. The analyses estimated differences in observed change among participants as allocated; no causal estimand was prespecified, and the non-randomized design leaves residual confounding. The principal clinical analyses used change scores because these were the analyses conducted before revision. Baseline-adjusted or mixed models were not represented retrospectively as prespecified analyses.

For each outcome, change scores were calculated as the difference between the post-intervention and baseline values (Δ = post-intervention value − baseline value). The distribution of change scores was assessed using the Shapiro–Wilk test.

Within-group pre–post comparisons were performed using paired Student’s t-tests for variables meeting the normality assumption and Wilcoxon signed-rank tests for variables that did not meet this assumption. These tests described temporal change within groups and were not interpreted as evidence of an intervention-specific effect. Between-group differences in change scores were assessed using the Kruskal–Wallis test. When the overall test indicated a difference (*p* < 0.05), pairwise Mann–Whitney U comparisons were performed for CST versus RT, CST versus CG, and RT versus CG. Binary NMQ symptom indicators were summarized as counts and proportions rather than analyzed as continuous change scores.

For salivary cortisol, for which the assumptions for parametric analysis were met, within-group changes were assessed using paired Student’s *t*-tests, while between-group differences in change scores were assessed using one-way analysis of variance (ANOVA), followed by Tukey’s post-hoc test where appropriate.

To account for multiple comparisons within related outcome families, Holm adjustment was applied separately to the family of sleep-related outcomes and to the family of spirometric and oscillometric outcomes. No multiplicity adjustment was applied across the complete set of exploratory clinical outcomes; consequently, unadjusted *p*-values outside these families are descriptive and not confirmatory.

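### NMQ-7, kept as the pre–post indicator for a registered secondary outcome, has no stated paired summary or between-arm estimate of change

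*Protocol article*

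**What the plan says.** All references are to the protocol article.

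- Section 2.8 makes musculoskeletal symptoms a registered secondary outcome: "Registered secondary outcomes included salivary cortisol concentration, myotonometric measures of tissue tone and stiffness, musculoskeletal symptoms". Section 1.3 says the same.
- Section 4 administers the NMQ "across nine body regions" and separates its two recall periods. For the short one: "NMQ-7 assessed symptoms during the previous 7 days and was treated as an exploratory pre–post symptom indicator". The six-month version "was excluded from analyses intended to represent change during the intervention". Table 3 repeats this split.
- Section 4 then says how the items are handled: "Binary symptom indicators were summarized using counts and proportions".
- Section 4.2 sets the quantities of interest for clinical outcomes: "The target exploratory contrasts were CST versus CG, RT versus CG, and CST versus RT for change from baseline to 8 weeks". It adds a general rule: "For each outcome, change scores were calculated", as the post-intervention value minus the baseline value.
- Later in section 4.2 the NMQ is taken out of that rule: "Binary NMQ symptom indicators were summarized as counts and proportions rather than analyzed as continuous change scores".

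No paired method, category of change or between-arm comparison is given for the NMQ items. The analysis entry in Table 3 for the secondary and exploratory outcomes names no method.

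**The concern.** Section 4.2 gives a rule for every outcome and a target for every clinical comparison. It then removes one registered secondary outcome from the rule without saying how the target is met for it. NMQ-7 is called a pre–post indicator, but the stated summary need not show change within a woman.

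This bears on what the pilot is for. Section 1.3 wants preliminary estimates with confidence intervals, and section 8 sees the study's value in identifying responsive measures, choosing outcomes and planning a sample size. For a paired yes/no outcome those uses rest on the discordant pairs: how many women lost a symptom and how many gained one. Prevalence at each visit does not contain that information.

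**Working it through.** The documents give no NMQ-7 result, so there is no figure of the plan's own to reproduce. The check asks what per-visit counts do and do not determine at the trial's group sizes.

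**Inputs from the protocol article**
- Group sizes: CST 12, RT 10, CG 10 (section 2.5).
- Nine regions (section 4) and three contrasts (section 4.2).
- No missing pre–post values, so every NMQ-7 pair exists (section 4.2).

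**Assumed inputs (one region, for illustration only)**
- CST: 8/12 symptomatic before, 5/12 after.
- CG: 7/10 before, 6/10 after.

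**Step 1: which pairings fit the margins.** Let n be the arm size, b the number positive before, a the number positive after, and k the number positive at both visits. Then k lies between max(0, a + b − n) and min(a, b). The number resolved is b − k and the number new is a − k.
- CST: k runs from 1 to 5, so resolved/new runs from 7/4 to 3/0.
- CG: k runs from 3 to 6, so resolved/new runs from 4/3 to 1/0.

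**Step 2: net change and its paired standard error.** With d = (new − resolved)/n, the Wald variance is [(resolved + new)/n − d²]/n.

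| Arm | Resolved/new | d | Variance | SE |
|---|---|---|---|---|
| CST | 3/0 | −0.25 | (0.2500 − 0.0625)/12 = 0.0156 | 0.125 |
| CST | 7/4 | −0.25 | (0.9167 − 0.0625)/12 = 0.0712 | 0.267 |
| CG | 1/0 | −0.10 | (0.10 − 0.01)/10 = 0.0090 | 0.095 |
| CG | 4/3 | −0.10 | (0.70 − 0.01)/10 = 0.0690 | 0.263 |

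The margins fix d within each arm. They do not fix its standard error, which more than doubles between the extreme pairings.

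**Step 3: the CST − CG contrast.** The point estimate is −0.25 − (−0.10) = −0.15 in every case.
- Fewest women changing: SE = √(0.0156 + 0.0090) = 0.157. The half-width is 1.96 × 0.157 = 0.31, and the 95% CI is −0.46 to 0.16.
- Most women changing: SE = √(0.0712 + 0.0690) = 0.374. The half-width is 1.96 × 0.374 = 0.73, and the 95% CI is −0.88 to 0.58.

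**Step 4: the volume of output.** Per-visit reporting gives 9 × 2 × 3 = 54 proportions for NMQ-7. The three contrasts in each region would give 9 × 3 = 27 estimates, none of which the article says were made.

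**The case against.** The strongest defence is that descriptive treatment is a deliberate, stated choice. NMQ-7 is labelled exploratory, as are all clinical analyses. The arms have 10 to 12 women, and no feasibility quantity depends on it. Section 4 says the NMQ captures occurrence and distribution, which regional counts describe. The article presents no clinical results, and a condensed article may leave the layout of a descriptive table to the results report. This stands as a limit on severity. It does not remove the point: section 4.2 states which analysis the NMQ received, and that analysis does not meet the target stated a few sentences before.

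Several stronger readings are tempting, and the documents do not support them.
- **That the counts are certainly separate before and after counts.** The text says only counts and proportions. Numbers resolved, new and persisting are also counts, so transitions may have been tabulated.
- **That no contrast can be obtained.** Even per-visit proportions give net change by arm and a crude point difference between arms. What is lost is the individual transitions and a valid interval.
- **That NMQ-7 is the only usable measure of the registered outcome.** It is the only NMQ version kept for change. Pain on the VAS is also measured at both visits, although section 4 keeps it apart from the NMQ and section 2.8 does not name it. The article does not say which instrument was registered for this outcome.
- **That the lack of a single symptom endpoint is a fault.** Nothing in the article calls for one. A count of symptomatic regions would be a new composite, made after the data were analysed, that weights all regions equally.

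**Conclusion.** The point holds in a limited form. Section 4.2 promises change contrasts between arms and change scores for every outcome, then gives the NMQ items counts and proportions alone. NMQ-7 is left without a stated paired summary or between-arm estimate, although it is the NMQ version reserved for pre–post use.

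The size of the loss depends on the per-visit reading, which is likely but not explicit. Under it, and with the assumed counts, the CST − CG point difference is known (−0.15), but its 95% half-width could be anything from about 0.31 to 0.73. The number of CST women who improved could be anything from 3 to 7. Other counts would give other ranges. If transitions were in fact tabulated, the defect shrinks to unclear wording and the missing between-arm estimate.

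Keeping yes/no items out of continuous change scores is right, and so is leaving NMQ-6 descriptive. Severity is low to moderate because every clinical analysis is exploratory.

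**What to change.** In section 4.2, replace the sentence on binary NMQ indicators with text that does the following:
1. States that the NMQ is an exception to the change-score rule.
2. For NMQ-7, reports by arm and region the paired transition counts: never symptomatic, resolved, new, persisting.
3. For the three contrasts already named, reports the between-arm difference in net change in proportion, with a 95% CI that uses the pairing. The Wald form above collapses to zero width when no woman in either arm changes, so a score-type interval is preferable at these sizes.
4. Labels these summaries exploratory and added at revision.
5. Leaves NMQ-6 descriptive.

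A change in the number of symptomatic regions (0 to 9) may be added, but it is optional.

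The cost is small: a few lines of R on complete pairs from 32 women. The summaries must carry a post hoc label, and the 27 intervals will be imprecise with 10 to 12 women per arm. They are simple tabulations, so they do not conflict with the article's decision against adding complex models retrospectively. If transitions were already tabulated, items 1 and 2 reduce to saying so.

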The assessment of these multidimensional outcomes is intended to explore potential patterns of change associated with CST and RT rather than to provide confirmatory evidence of intervention effectiveness. The resulting preliminary estimates may help identify potentially responsive outcome measures and inform the methodological design, outcome selection, and sample-size planning of a future adequately powered randomized controlled trial.

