### 2.3. Eligibility Criteria

The study included mothers aged 25 to 44 years who were raising one child with a congenital disability and who had held an official disability certificate for at least two years.Recruitment of mothers of children with disabilities was conducted through healthcare facilities, schools for children with disabilities, and information was disseminated via Facebook social media platforms.Eligibility also requires written informed consent. The original study records used the phrase ‘generally good health’ and a participant declaration of no exclusion criteria but did not provide a sufficiently operationalized list in the materials available for this revision; these vague criteria are not presented as reproducible eligibility rules.Participants were required to have a raw WHO-5 score below the maximum possible score (<25 on the 0–25 raw scale) and either mild musculoskeletal pain (VAS 1–4 on a 0–10 scale) or tension-related complaints and/or reduced mobility identified during functional assessment. The WHO-5 criterion indicated less than maximal self-reported well-being and was not a diagnostic threshold for stress or mental disorder.

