Effect sizes were calculated to complement statistical significance testing. Standardized mean change was calculated as d = mean(Δ)/SD(Δ), and rank-biserial correlation (r) was calculated where appropriate. Effect estimates and 95% confidence intervals are intended for the reporting of clinical results, where supported by the corresponding estimators. No clinical outcome results are presented in this protocol report. Given the small sample, all clinical estimates and *p*-values were interpreted cautiously and within an exploratory framework. No confounder-adjusted model or formal sensitivity analysis was prespecified; additional complex models were not introduced retrospectively. Age and baseline outcome value are identified as priorities for a future adequately powered trial.

All 32 enrolled participants contributed to the feasibility analysis and completed 8-week outcome assessment; no pre-post values were missing. The analysed clinical sample therefore equalled the full enrolled sample. No imputation, per-protocol exclusion, outlier exclusion, treatment-discontinuation analysis, or missing-data sensitivity analysis was required or performed.

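### The only standardized mean effect size defined in section 4.2 is a within-arm pre-post d, which estimates none of the stated between-group contrasts and would missize a future trial if used for planning

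*Protocol article*

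**What the plan says.** All places are in the protocol article.

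- **Target (section 4.2).** "The target exploratory contrasts were CST versus CG, RT versus CG, and CST versus RT for change from baseline to 8 weeks".
- **Change score (section 4.2).** Defined per participant as "Δ = post-intervention value − baseline value".
- **Between-group analysis (section 4.2).** Change scores are compared by a Kruskal–Wallis test. Pairwise Mann–Whitney tests follow only when the overall p-value is below 0.05. Cortisol uses ANOVA with Tukey's test. No between-arm estimator is named for any of these routes.
- **Effect size (section 4.2).** "Effect sizes were calculated to complement statistical significance testing". The definition follows: "Standardized mean change was calculated as d = mean(Δ)/SD(Δ), and rank-biserial correlation (r) was calculated where appropriate". The text does not say whether r belongs to the signed-rank test (within arm) or the Mann–Whitney test (between arms).
- **Caveat on the within-group tests (section 4.2).** "These tests described temporal change within groups and were not interpreted as evidence of an intervention-specific effect". The caveat is not repeated for d.
- **Intended use.** Section 1.3 says that the clinical analyses should yield preliminary estimates of intervention effects with confidence intervals. Section 1.2 says that the estimates may "inform the methodological design, outcome selection, and sample-size planning of a future adequately powered randomized controlled trial", and section 8 again lists sample-size planning as part of the study's value.
- **Table 3.** The registered primary clinical outcomes (spinal mobility and maximal inspiratory pressure) are to have pre-post and between-group estimates, again without a named estimator.

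**The concern.** The target and the effect size do not match. The target is a difference in change between arms. The one mean-based effect size with a formula is the change within one arm, divided by the SD of that change. It includes whatever would have happened without the intervention: natural change over eight weeks, familiarity with the tests, expectation and contact with the therapist. Section 8 itself says that the non-specific part cannot be separated from the specific part in this design. The article declines to read the within-group tests as evidence of an intervention-specific effect, yet it gives no such warning for the effect size built from the same quantity.

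What is at stake is the next trial. A reader who wants a planning effect would find d as the only standardized mean effect with a formula. If it were entered as a between-arm effect, the sample size would be wrong by an amount that depends on how the control arm changed.

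**Working it through.** **Inputs from the article.** Δ and d as defined in section 4.2; arm sizes 12 (CST), 10 (RT) and 10 (CG) from section 2.5. Section 2.5 says that no sample-size calculation was made, and section 4.2 says that no clinical results are presented. There is therefore no planned figure to reproduce, and no observed d to correct.

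**Inputs assumed for illustration.** Two-sided alpha 0.05, 80% power, 1:1 allocation, normal approximation, SD(Δ) equal in the two arms, within-arm d = 0.5, and a range of control-arm changes c in SD(Δ) units.

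**Step 1: what d estimates.** For an active arm A and comparator C with a common SD(Δ), the between-arm effect on the change scale is

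δ = (mean Δ_A − mean Δ_C) / SD(Δ) = d_A − d_C.

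So d_A equals δ only if d_C = 0. If the two SDs differ, the equality fails in general even then. For CST against RT, the comparator is itself treated, so zero change in it is a still less natural assumption.

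**Step 2: sample size if d is taken for δ.** The number per arm is 2(1.96 + 0.842)² / δ² = 15.70 / δ².

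- δ = 0.5: 15.70 / 0.25 = 62.8, so 63 per arm.
- δ = 0.3 (c = 0.2): 15.70 / 0.09 = 174.4, so 175 per arm.

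Power at 63 per arm when δ = 0.3: 0.3 × √(63/2) = 1.684; 1.684 − 1.96 = −0.276; Φ(−0.276) = 0.39.

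**Step 3: range over the control change.**

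| Control change c | True contrast 0.5 − c | Needed per arm | Power with 63 per arm |
|---|---|---|---|
| −0.2 | 0.7 | 33 | 98% |
| 0 | 0.5 | 63 | 80% |
| 0.1 | 0.4 | 99 | 61% |
| 0.2 | 0.3 | 175 | 39% |
| 0.3 | 0.2 | 393 | 20% |

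The error disappears at c = 0 and reverses when controls worsen.

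**Step 4: is the denominator also wrong?** With raw-score SD equal to 1 at both visits and pre-post correlation ρ, SD(Δ) = √(2(1 − ρ)). At an assumed ρ = 0.8 this is 0.63. The residual SD of a baseline-adjusted analysis is √(1 − ρ²) = 0.60. SD(Δ) is thus the right denominator for a change-score comparison and close to the right one for a baseline-adjusted analysis. Sizing such a trial on the raw SD would oversize it by 1/0.40 = 2.5-fold or 1/0.36 = 2.8-fold respectively. The defect is the missing control term.

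**Step 5: precision of the quantity that is needed.** An observed 0.5 has a 95% interval (noncentral t) of about −0.11 to 1.09 within CST (n = 12) and −0.36 to 1.35 between CST and CG (12 against 10). The between-arm estimate is less precise, and a plan for the next trial has to face that uncertainty.

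**The case against.** The strongest reply is that nothing in the article makes d a treatment effect or a planning input. Its stated role is to complement the significance tests, and the planning statements in sections 1.2 and 8 concern the estimates or data in general. Table 3 lists between-group estimates, r may be a between-group measure, all clinical results are exploratory, and an article may leave the between-arm estimator to a fuller plan. Much of this stands: harm arises only if d is used as a between-arm effect. It does not remove the mismatch, because the formula is stated, as one already used, and it does not correspond to the stated contrasts.

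A reader might infer four stronger points, which the documents do not support:

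- **That the next trial will be undersized.** No section commits to using d for planning, and Step 3 shows that the error can go either way.
- **That SD(Δ) is the wrong scale.** It would be wrong only for a trial that analyses unadjusted post-intervention scores. This study analyses change scores, and section 4.2 names baseline outcome value as a priority for the future trial.
- **That regression to the mean in spinal mobility inflates d.** Mothers could qualify through "tension-related complaints and/or reduced mobility identified during functional assessment", but mild pain was an alternative route and no cut-off on the spinal mobility device is stated. Selection on that outcome is possible but not shown.
- **That the normality check sends different arms to different tests.** Section 4.2 prescribes "Wilcoxon signed-rank tests for variables that did not meet this assumption", which may well mean one choice per variable for all arms. A mixed route requires a per-arm reading that the text does not state.

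The lack of a stated small-sample correction for d is a detail that an article may leave out.

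**Conclusion.** The point holds as a mismatch between estimator and target. The only standardized mean effect size with a formula is a within-arm quantity. It estimates none of the three contrasts and in general equals one of them only if the comparator does not change and SD(Δ) is equal across arms. Its consequence is conditional: if d were used to size a later trial, the sample size could be too small or too large. Under the assumptions above, a control change of 0.2 SD(Δ) turns an apparent requirement of 63 per arm into 175, with about 39% power at 63. The actual size cannot be known, because the article gives no d, no SD and no control-arm change.

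The correction is worth making. It is not critical to the study's main purpose, since feasibility is primary and the clinical analyses are exploratory.

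**What to change.** In section 4.2:

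1. For each of the three contrasts and every continuous outcome, report the between-arm difference in mean change with a 95% confidence interval, whatever the Kruskal–Wallis result. If a standardized version is wanted, divide by the pooled SD(Δ) and apply a Hedges correction.
2. Report baseline SD, SD(Δ) and the pre-post correlation for each outcome, so that a future trial can be sized for its own analysis.
3. Label the within-arm d as descriptive of change over time, and say that it is not a planning effect.
4. State which test the rank-biserial r belongs to.
5. Label the added estimates post hoc, since the analyses were complete before this version. They remain unadjusted for confounding in a non-randomized comparison.

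The cost is a few sentences and a recalculation from existing data, which the article describes as complete for all 32 participants. These are simple estimates of contrasts already named, so they do not conflict with the decision against adding complex models retrospectively. The downside is wide intervals and possibly smaller effect sizes.

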### 2.5. Sample Size

No formal priori sample size calculation was performed because the study was designed as a pilot and feasibility project conducted within the framework of a time-limited institutional mini-grant. The sample size was therefore determined pragmatically based on recruitment feasibility, available project resources, and the capacity to deliver the interventions within the project timeframe. In particular, the CST intervention required eight individual 60 min sessions per participant, delivered once weekly over eight consecutive weeks by the same therapist, which limited the number of participants who could feasibly complete the intervention during the funding period. The final sample comprised 32 participants: 12 in the CST group, 10 in the respiratory training group, and 10 in the control group. Accordingly, the study was not powered to provide confirmatory evidence of intervention effectiveness, and analyses of clinical outcomes should be interpreted as exploratory.

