Despite these limitations, the study provides a structured framework for evaluating two distinct non-pharmacological interventions in mothers of children with disabilities. The collected data may provide preliminary estimates and help identify potentially responsive outcome measures for future research. The study does not provide confirmatory evidence of intervention effectiveness or safety; its principal value is to inform future methodological procedures, outcome selection, documentation standards, and sample-size planning.

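### The standardized mean change d = mean(Δ)/SD(Δ) has no small-sample correction, so with 10 to 12 women per arm it is biased away from zero on average by about 7.5% to 9.4%: a minor bias, easily removed.

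*Protocol article*

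**What the plan says.** Section 4.2 (Statistical Analysis) gives the estimator in full: "Standardized mean change was calculated as d = mean(Δ)/SD(Δ), and rank-biserial correlation (r) was calculated where appropriate". For the input Δ, the same section says that "change scores were calculated as the difference between the post-intervention and baseline values", so d is a one-sample, within-arm quantity. On arm sizes, Section 2.5 states: "The final sample comprised 32 participants: 12 in the CST group, 10 in the respiratory training group, and 10 in the control group". Section 4.2 reports no missing pre-post values and concludes: "The analysed clinical sample therefore equalled the full enrolled sample". The degrees of freedom are therefore 11, 9 and 9.

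On use, Section 8 says of the study that "its principal value is to inform future methodological procedures, outcome selection, documentation standards, and sample-size planning"; the end of Section 1.2 also names sample-size planning. On caution, Section 4.2 says that clinical estimates were "interpreted cautiously and within an exploratory framework". It adds that 95% confidence intervals are intended where the estimator supports them, and that this article presents no clinical results.

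**The concern.** The sample SD is in the denominator. At small n the average of 1/SD is larger than 1/σ, so mean(Δ)/SD(Δ) lies further from zero, on average, than the true standardized change. This is a property of the formula as written; it does not depend on anything an unseen analysis plan might add. The same formula and the same small arms serve every continuous outcome for which d is given, so the bias does not average out across outcomes. Anyone who carries these values into the planning of the next trial starts from a figure that is, in expectation, somewhat too optimistic.

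**Working it through.** The article gives no d value, power or target effect to reproduce. Section 2.5 explains that no calculation was made "because the study was designed as a pilot and feasibility project conducted within the framework of a time-limited institutional mini-grant". The check therefore starts from the stated formula and arm sizes.

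**Inputs**
- n = 12 (CST), 10 (RT), 10 (CG): Section 2.5.
- Analysed n equals enrolled n: Section 4.2. Hence m = n − 1 = 11, 9, 9.
- d = mean(Δ)/SD(Δ): Section 4.2.
- Assumption: SD uses divisor n − 1, the usual default in the software named in Section 4.2 ("Statistical analyses were performed in R 4.3.2 after study completion").
- Assumption: Δ is approximately normal within each arm.

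**Formula.** Under normality, √n·d follows a noncentral t distribution with m degrees of freedom and noncentrality √n·δ, where δ is the true standardized change. Its mean gives

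E[d] = δ / J(m), with J(m) = Γ(m/2) / [√(m/2) · Γ((m − 1)/2)].

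**Numbers in**
- m = 9: J = Γ(4.5)/[√4.5 · Γ(4)] = 11.632/(2.1213 × 6) = 0.914. Expected inflation 1/J − 1 = 9.4%.
- m = 11: J = Γ(5.5)/[√5.5 · Γ(5)] = 52.343/(2.3452 × 24) = 0.930. Expected inflation = 7.5%.
- The approximation J ≈ 1 − 3/(4m − 1) gives 0.9143 and 0.9302, hence 9.4% and 7.5% again.
- A simulation with 1,000,000 replicates per n at δ = 0.5 gave 9.6% and 7.4%, in agreement within simulation error.

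**Size against noise, at an assumed true δ of 0.5**

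| | n = 12 (CST) | n = 10 (RT, CG) |
|---|---|---|
| E[d] uncorrected | 0.538 | 0.547 |
| Bias | 0.038 | 0.047 |
| Sampling SD of d | 0.344 | 0.388 |
| Bias / SD | 0.11 | 0.12 |
| Median of d | 0.512 | 0.515 |
| Probability that d exceeds δ | 0.515 | 0.517 |

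At δ = 0 the bias is zero. Between arms, J(11)/J(9) − 1 = 1.8%; RT and CG share one factor.

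**Effect of the correction on one value.** An observed d of 0.50 becomes 0.50 × 0.914 = 0.46 at n = 10 and 0.50 × 0.930 = 0.46 at n = 12 (0.457 and 0.465 before rounding). The noncentral-t 95% interval for δ is −0.17 to 1.15 at n = 10 and −0.11 to 1.09 at n = 12.

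**The case against.** The strongest reply is that this is a preference about a descriptive statistic. Uncorrected d is in common use, the article prints both its formula and the arm sizes, and any reader can apply J in one step. The article repeatedly calls the clinical estimates exploratory, plans confidence intervals and prints no d. The bias is also small beside the sampling error. Most of this stands, and it is why the point is minor. What it does not answer is direction: cautious reading deals with random error, whereas this is a known bias with a closed-form correction.

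A reader might infer four stronger things, none of which the documents support.

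- *Every reported effect is overstated by 7.5–9.4%.* The bias holds only in expectation. At a true d of 0.5, about 48% of observed values fall below the truth. Section 4.2 also expects some variables to fail normality, and the factor J is not exact for those.
- *Comparisons between arms are distorted.* Only CST differs from the other two, by 1.8%, or about 0.009 at a true d of 0.5.
- *The next trial will be 13.5–16.5% too small* (1 − J², since required n scales with 1/d²). That needs someone to put a within-arm pre-post d into a between-arm calculation. The article does not say that this will be done, and doing so would be a larger error than omitting J.
- *A between-arm d is inflated too.* The article defines no between-arm d. Section 4.2 compares arms by rank tests, with analysis of variance for cortisol.

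**Conclusion.** The point holds as a minor one. The stated estimator is biased away from zero in expectation by about 7.5% at n = 12 and 9.4% at n = 10, given approximately normal Δ and an n − 1 SD. The bias is proportional to the true change, is only about 2–3% on the median scale, and is about one eighth of the sampling SD at a true d of 0.5. It leaves p-values, rank tests, rank-biserial r and the feasibility proportions as they are. It contradicts nothing in the article and changes no conclusion there. It is worth removing because its direction is known and the estimates are offered as material for later planning. Grade: optional.

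**What to change.** When the clinical results are reported, multiply each standardized mean change by J(n − 1), that is 0.930 for CST and 0.914 for RT and CG, for outcomes where Δ is approximately normal. Give a noncentral-t 95% confidence interval with each. That interval already refers to δ and is not itself multiplied by J. Label the value as small-sample corrected and as a within-arm quantity that should not be used directly as a between-arm planning effect. If the authors prefer to keep d as computed, they should state that it is uncorrected.

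The cost is about one line of code per effect size and slightly smaller reported values. No new data or model is needed, so it does not cut across the authors' decision in Section 4.2 not to add complex models after the fact.
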